## Abstract

Supplemental Digital Content is available in the text

## Introduction

1

Stroke is the second most common cause of death in the world and generates high levels of functional incapacity in the chronic phase.^[1]^

Stroke provokes innumerable alterations in motor function, and hemiplegia is the most frequent manifestation after the event.^[2]^ Several studies have revealed that muscular strength and tonus present modifications after stroke according to the location and severity of the injury to the cerebral tissue.^[3]^ Besides these alterations, impairments in the visual, vestibular, and sensorial systems as well as coordination may also be present in these individuals.^[4]^

Thus, the modifications caused after stroke in hemiplegic individuals are also reflected in gait execution, which presents a marked reduction in velocity, postural asymmetry, and disturbances in balance and in postural control.^[5]^

The incapacities and diverse modifications resulting from stroke require that affected individuals make substantial adaptations in order to deal with the situation.^[6,7]^ The presence of depression in this population is very frequent, and in many cases, depression can impede adherence to treatment and progress for these individuals.^[8]^

Gait deficits present a negative impact on post-stroke functional capacity by impairing the perception of these individuals in relation to their functionality and social participation as well as potentially leading to prejudice about their quality of life in this population.^[9,10]^ A study of individuals after stroke demonstrated that functionality and mobility, when they are impaired, negatively influenced life quality, and the individuals with diminished velocity and quality of gait presented worse quality-of-life scores.^[11]^

One of the assistive technology resources employed by physiotherapy to optimize the gait after stroke is the ankle-foot orthosis (AFO). It is an external device utilized on a lower limb to stabilize the joints and provide a more adequate gait. It may be prescribed in any period of rehabilitation and can be substituted or modified according to necessity or evolution.^[12]^

The first references to the use of thermoplastic materials in the construction of orthoses for lower limbs were published at the end of the 1960s by the pioneers Yates and Lehneis.^[13,14]^ Lehneis et al studied the biomechanics of thermoplastic AFO and recognized the enormous potential of using these materials in orthoses for lower limbs.^[15]^ Over the years, the models and application of AFOs have continued to evolve, including the ones that are currently in use.^[16]^

One of the principal post-stroke problems during gait is equinus deformity, which is generally associated with spasticity and shortening of the sural triceps and results in dorsiflexion reduction.^[17]^ Spasticity of the sural triceps can also lead to another abnormal manifestation during gait, specifically hyperextension of the knee in the support phase. This manifestation can also be minimized via the use of AFO orthosis, which diminishes the hyperactivity of the sural triceps upon neutralizing the foot and cooperates in the correction of equinus deformity and knee hyperextension.^[18]^ Furthermore, it presents improvement in balance and diminishes fall risks in patients who present signs of hemiplegia.^[19]^

The 2 types of AFO orthoses most often prescribed after stroke are Fixed AFO and Articulated AFO. The Fixed AFO is indicated to eliminate excessive plantar flexion and minimize hyperextension of the knee.^[18]^ It is also utilized to prevent joint deformities in non-ambulatory patients.^[12]^

The Articulated AFO provides aid in dorsiflexion, blocking the ankle in an adequate position; by being articulated, it permits ankle movements, unlike Fixed AFO, which neutralize this joint, and it also corrects a hyperextended knee.^[20]^ Nevertheless, there are few studies that have evaluated the use of different types of AFO orthoses in stroke patients. The prescription of the AFO-type orthosis for these patients ends up occurring frequently by professionals due to the small number of studies available on this topic.

Due to their high incapacitating potential, strokes have a great impact on public health^[21]^; therefore, more studies are necessary to verify the most efficacious treatments for this population. In relation to the type of AFO for this condition, the literature offers little information. Specifically, more research studies are necessary to determine which orthosis presents greater efficacy in this pathology. Our main hypothesis is that the distinct AFO types differ in the recovery of motor performance in patients after stroke. We hypothesized that Fixed AFO improves hemiplegic gait, but by not limiting the normal movements of the ankle, Articulated AFO would be more beneficial in the rehabilitation of these patients.

## Objective

2

We aim to evaluate the impact of the type of AFO orthosis on motor function and gait in individuals after a stroke. We will also investigate the relationship between the prescribed AFO orthosis type and life quality, anxiety, and depression.

## Methods/design

3

### Trial design

3.1

This single-center, open, randomized, controlled clinical trial with parallel groups of 50 patients after stroke will be conducted according to the flow diagram and will last for 12 months, scheduled to start in May 2019 (Fig. 1).

**Figure 1 F1:**
[figure not shown]
Study flowchart.

### Location and setting

3.2

All assessments will be conducted at the Botucatu Medical School within the Department of Neurology and Center of Rehabilitation, Botucatu, Brazil.

### Participants

3.3

#### Eligibility criteria

3.3.1

The patients recruited for the study will be recruited from the Rehabilitation Sector of the Hospital of Clinics at the UNESP Botucatu Medical School, and the inclusion criteria will be verified.

The patients who have an indication for the use of both AFO types are those with hemiplegia or hemiparesis who present diminished walking ability, postural control alterations, diminished joint mobility (principally in dorsiflexion), balance disorders, muscular tonus alterations with varo-equinus deformities, presence of knee hyperextension in the support phase and impairment of proprioception in some cases.^[22]^

The inclusion criteria for the study are as follows:Individuals of either sex who can utilize both types of orthoses in treatment;Less than 1 year from stroke;A previous Rankin score of less than or equal to 3;An indication of AFO orthosis after evaluation of ambulatory rehabilitation at the Hospital Clinics at the UNESP Botucatu Medical School.

#### Exclusion criteria

3.3.2

Individuals with amputation of a lower limb and/or being a carrier of a progressive neuromuscular disease.

#### Discontinuing criteria

3.3.3

Any patients who do not use the orthosis and/or have dermatitis in the hemiplegic leg.

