### Procedures (Template)

3.4

Post-stroke patients will be evaluated by a physiotherapist and a physician with experience in the evaluation and prescription of AFOs. After evaluation by the team, the patients who have an indication for the use of AFO orthosis and fit the eligibility criteria of the study will be referred for specific evaluation. All the participants will sign terms of free and informed consent for participation in the study.

The individuals who fit the criteria for inclusion in this study will be randomized to receive 1 of the 2 types of orthoses: Fixed AFO or Articulated AFO.

The first evaluation will occur before the patient begins the use of AFO orthosis, and then the patient will be reevaluated 30 days after the intervention (AFO use).

All the scales, questionnaires, and tests that will be applied were already translated, adapted and validated for the Portuguese language used in Brazil. Individuals will be assessed using the Time Up Go Test (TUG), Tinetti's Scale of Mobility and Balance (TSMB), European (5D) Quality of Life Scale (Euroqol), Hospital Anxiety and Depression Scale (HADS), modified Rankin scale (mRs), National Institute of Health Stroke Scale (NIHSS), Barthel Index (BI), and the Modified Scale of Ashworth (mAS).

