### Intervention

3.6

After specific evaluation by a physiotherapist, the patient will receive 1 of the 2 types of AFOs according to the randomization either Fixed or Articulated.

Group 1: Fixed AFO

The Fixed AFO orthosis neutralizes the ankle by blocking movements, eliminating excessive plantar flexion, and minimizing knee hyperextension in the medial support phase.^[18]^

Group 2: Articulated AFO

Articulated AFO orthosis provides aid in dorsiflexion, leaves the ankle in an adequate position, and allows its movement by virtue of being articulated.^[20]^

The patients will be instructed about the correct placement and use of the orthosis; furthermore, a member of the team will make weekly telephone contact to verify adherence to the treatment. After 30 days, the patient will be reevaluated by applying the scales and tests that were previously mentioned.

All patients underwent physiotherapy during the study period.

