### Sample size calculation

3.9

The sample will be composed of 50 volunteers randomized into 2 groups to receive 1 of 2 types of AFO. This number of participants are capable to detecting a 30% difference in improvement of the primary outcome (TUG and TSMB) with an alpha error of 0.05 and beta error of 0.2.

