### Statistical analysis

3.13

The analyses will follow the principle of Intention to Treat. The Kolmogorov-Smirnov test will be employed to verify the normality of the distribution. The non-categorical data of a parametric distribution will be analyzed by two-way ANOVA for repeated measures, and multiple comparisons will be analyzed with the Tukey test. The categorical data at the baseline moment will be compared using the Chi-Squared test. The nonparametric distribution variables will be categorized as improvement or worsening and compared between groups with the Chi-Squared test. The non-categorical data will be expressed as means and standard deviations, and the categorical data will be expressed as percentages. Statistical significance will be established as *P* < .05.

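### The discontinuing criteria (non-use, dermatitis) are not reconciled with the promised intention-to-treat analysis, and the day-30 visit has no clear date for a patient who never starts the orthosis

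*Protocol article*

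**What the plan says.** Section 3.3.3 (Discontinuing criteria) consists of one line: "Any patients who do not use the orthosis and/or have dermatitis in the hemiplegic leg". It does not say what is discontinued: the orthosis, follow-up, or inclusion in the analysis.

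Section 3.13 (Statistical analysis) states: "The analyses will follow the principle of Intention to Treat".

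The outcome visit is described twice. Section 3.4 (Procedures) says "then the patient will be reevaluated 30 days after the intervention (AFO use", so the clock runs from orthosis use. Section 3.6 (Intervention) says "After 30 days, the patient will be reevaluated by applying the scales and tests that were previously mentioned", with no condition on wear and no stated starting point. Section 3.6 also provides for adherence checks: "a member of the team will make weekly telephone contact to verify adherence to the treatment".

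Section 3.9 plans 50 patients and section 3.5 allocates 25 to each group. The sample size text mentions no allowance for loss.

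**The concern.** Intention to treat keeps non-adherent and intolerant patients in the arm to which they were allocated. Section 3.3.3 names exactly those patients and discontinues them. One device blocks the ankle and the other lets it move, so wear and skin tolerance may well depend on the device. The trial is open and adherence is checked weekly, so staff will identify non-users with the allocation known.

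If patients who meet 3.3.3 are not measured at day 30, each arm is represented by those who wore and tolerated their device. Should one device be worn less or irritate more, its failures drop out of the comparison and that arm looks better than it is. The trial is meant to guide which orthosis is prescribed, and wearability is part of that question. A day-30 value that was never measured cannot be recovered later.

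**Working it through.** **1. What does discontinuing mean?** The milder reading is that only the orthosis is stopped. That could fit dermatitis. It fits non-use poorly, because a patient who does not use the orthosis has no use left to stop. The rule also stands under 3.3 (Participants), directly after the inclusion and exclusion criteria, and not under 3.6 (Intervention). The natural reading, at least for non-users, is therefore departure from the study. No sentence confirms or rules this out.

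**2. Does every randomised patient have a day-30 date?**

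| Patient | Section 3.4 (from orthosis use) | Section 3.6 (after 30 days) |
|---|---|---|
| Wears the device throughout | defined | defined |
| Starts, then stops | defined | defined |
| Never starts | no clear date | visit due, starting point not stated |

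The gap is confined to never-starters.

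**3. Possible bias if discontinued patients go unmeasured.** The documents give no discontinuation rates, so every rate here is an assumption. Let change be standard normal with no true difference between arms. Let a fraction q of an arm be discontinued through a normal liability with correlation ρ to poor change. The mean of those retained then shifts upwards by

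shift(q) = ρ · φ(z_q) / (1 − q),

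where φ is the standard normal density and z_q the q-quantile. The bias is the difference between the arms' shifts. With ρ = 0.5:

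- q = 20% (5 of 25): 0.5 × 0.2800 / 0.80 = 0.175
- q = 12% (3 of 25): 0.5 × 0.2000 / 0.88 = 0.114
- q = 4% (1 of 25): 0.5 × 0.0862 / 0.96 = 0.045

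| Loss, arm A vs arm B | Bias in favour of A |
|---|---|
| 20% vs 4% | 0.175 − 0.045 = 0.13 SD |
| 12% vs 4% | 0.114 − 0.045 = 0.07 SD |
| 10% vs 10%, same mechanism | 0 |

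The result scales with ρ. At 20% vs 5% loss it is 0.07 SD for ρ = 0.3, 0.12 SD for ρ = 0.5 and 0.24 SD for ρ = 1. In simulated trials of 25 per arm with ρ = 0.5 (8,000 per scenario), the two-sided 5% t-test rejected a true null in 6.4% of trials at 20% vs 5%, 7.7% at 30% vs 10%, and 4.8% at 10% vs 10%.

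**4. Loss of power.** Section 3.9 gives alpha 0.05 and beta 0.2 but neither an SD nor a control rate, so the planned 50 cannot be reproduced. As a reference I take the standardised difference that 25 per arm detects with 80% power, two-sided, by the normal approximation: (1.960 + 0.842) × √(2/25) = 0.79 SD. Power with n per arm is Φ(0.79/√(2/n) − 1.96), using the unrounded 0.7924:

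- 10% loss in both arms, n = 22.5: Φ(2.658 − 1.960) = 75.7%
- 20% loss in both arms, n = 20: Φ(2.506 − 1.960) = 70.7%

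By the noncentral t, the detectable difference is 0.81 SD at 25 per arm, 0.87 at 22 and 0.91 at 20.

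**The case against.** The strongest reply is that the article never says discontinued patients go unmeasured or are left out of the analysis. Its only sentence on who is analysed commits to intention to treat, and discontinuing may mean no more than taking off the device. Section 3.6 provides a 30-day reevaluation that does not depend on wear. All this stands. A reader might infer that intention to treat cannot be carried out, or that the arms will in fact be compared on selected tolerators. The text supports neither as a statement of fact.

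A reader might also infer, from "The non-categorical data of a parametric distribution will be analyzed by two-way ANOVA for repeated measures", that anyone without both visits is dropped. Naming that method does not fix how missing visits are handled. That is commonly left to an analysis plan, which is not shown, and is no part of this point. Nor would a mixed model or multiple imputation in standard form cure the mechanism modelled above, where loss depends on the patient's own unobserved change. Measuring the patients does.

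The figures are assumed and modest. The standard error of a 25-versus-25 difference is √(2/25) = 0.28 SD, so 0.13 SD is under half a standard error and about one sixth of the 0.81 SD detectable difference. Eligibility requires that patients can use both orthosis types, which may limit unequal non-use. This also stands. It limits the likely size of the harm but does not reconcile the two sections.

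**Conclusion.** The point holds as an unreconciled conflict between sections 3.3.3 and 3.13, together with a visit date in 3.4 that is unclear for never-starters. It does not hold as proof that the trial abandons intention to treat.

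The consequence is conditional. If patients who meet 3.3.3 are not measured at day 30, the analysis is per-protocol in effect. The bias then depends on how unequal the loss is and how strongly it relates to outcome, neither of which the documents give: about 0.13 SD at 20% vs 4%, 0.07 SD at 12% vs 4%, and nil at equal loss with the same mechanism, all at an assumed correlation of 0.5. Power is lost in each case; with equal loss and the same mechanism, the cost is power and generalisability only. If discontinuing means only that the device is stopped and patients are still measured and analysed as allocated, no bias arises from this source, but the protocol needs to say so.

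**What to change.** Reconcile 3.3.3, 3.4 and 3.13 by stating that:

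- meeting a criterion in 3.3.3 does not end study participation;
- these patients have the day-30 assessment, dated from an event defined for every randomised patient (for example the planned fitting date), with the same window in both arms;
- they are analysed in their allocated group;
- non-use and dermatitis are reported by arm.

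Sections 3.4 and 3.6 should then give the same starting point for the 30 days. When a patient stops wearing the orthosis remains a clinical decision and is not changed by any of this.

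The cost is a few sentences and a few extra day-30 visits for patients already telephoned weekly. Section 5 (Trial status) reports recruitment as under way at submission, so the change cannot recover day-30 data from any patient already discontinued and not measured. The number of such patients should be reported by arm.

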### Procedures (Template)

3.4

Post-stroke patients will be evaluated by a physiotherapist and a physician with experience in the evaluation and prescription of AFOs. After evaluation by the team, the patients who have an indication for the use of AFO orthosis and fit the eligibility criteria of the study will be referred for specific evaluation. All the participants will sign terms of free and informed consent for participation in the study.

The individuals who fit the criteria for inclusion in this study will be randomized to receive 1 of the 2 types of orthoses: Fixed AFO or Articulated AFO.

The first evaluation will occur before the patient begins the use of AFO orthosis, and then the patient will be reevaluated 30 days after the intervention (AFO use).

All the scales, questionnaires, and tests that will be applied were already translated, adapted and validated for the Portuguese language used in Brazil. Individuals will be assessed using the Time Up Go Test (TUG), Tinetti's Scale of Mobility and Balance (TSMB), European (5D) Quality of Life Scale (Euroqol), Hospital Anxiety and Depression Scale (HADS), modified Rankin scale (mRs), National Institute of Health Stroke Scale (NIHSS), Barthel Index (BI), and the Modified Scale of Ashworth (mAS).

### Randomization and blinding

3.5

The process of randomization will be performed using Microsoft Excel for Windows by a researcher who was not involved in the recruitment of participants. The participants will be randomized into 2 groups at a proportion of 1:1 with 25 patients allocated into each group. After evaluation, the participants who are eligible for the study will be referred to a physiotherapist responsible for their specific evaluation.

Because of the nature of the interventions, it will be impossible to blind the therapists and patients involved in the study.

### Intervention

3.6

After specific evaluation by a physiotherapist, the patient will receive 1 of the 2 types of AFOs according to the randomization either Fixed or Articulated.

Group 1: Fixed AFO

The Fixed AFO orthosis neutralizes the ankle by blocking movements, eliminating excessive plantar flexion, and minimizing knee hyperextension in the medial support phase.^[18]^

Group 2: Articulated AFO

Articulated AFO orthosis provides aid in dorsiflexion, leaves the ankle in an adequate position, and allows its movement by virtue of being articulated.^[20]^

The patients will be instructed about the correct placement and use of the orthosis; furthermore, a member of the team will make weekly telephone contact to verify adherence to the treatment. After 30 days, the patient will be reevaluated by applying the scales and tests that were previously mentioned.

All patients underwent physiotherapy during the study period.

### Primary outcome measures

3.7

The primary outcomes will be balance and mobility, which will be evaluated by the TUG and by TSMB. These outcomes will be assessed after the intervention.

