## Discussion

4

Stroke is the principal incapacitating disease in adults,^[1]^ and the importance of optimizing strategies to rehabilitate patients affected by this disease is evident. Mobility improvement is the primary objective for most patients and therapists since it is essential for the independence of these individuals.^[31]^

Several studies have shown that AFO use produced improvement in the cadence and velocity of the gait by minimizing knee hyperextension along with improvements in symmetry and stability in these patients.^[32]^ Although there are some studies that report efficacy of AFO in these hemiplegic patients, research on its effects in relation to mobility, and to balance is scarce^[33]^; furthermore, there is no consensus on which AFO model is more efficacious for treating this pathology.

The results of this study will contribute to clinical practice by identifying the type of AFO orthosis that is more suitable for this condition, helping to standardize prescription of these orthoses by professionals, and guiding future research studies on this subject, which is still incompletely defined in the literature.

Our goal is to accomplish a randomized clinical trial of high quality that utilizes validated evaluation measures not only for balance and mobility in our primary outcomes but also for the levels of anxiety and depression in our secondary outcomes. If 1 of the AFO types is proven to be superior to the other in some of these aspects, this evidence would permit professionals to recommend the ideal AFO for patients with stroke sequelae, which will minimize their incapacity and optimize their rehabilitation. For our results to generate an impact on the clinical practice of therapists and on patient care, they should be publicized at congresses and in academic journals pertaining to this research area.

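### Two primary outcomes are each tested at 0.05 with no rule across them: if either one suffices, the false-positive rate is about 7% to 10%; if both are required, power is below 80%.

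*Protocol article*

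**What the plan says.** - **Primary outcome measures (3.7):** "The primary outcomes will be balance and mobility, which will be evaluated by the TUG and by TSMB". The two instruments are listed without order.
- **Sample size calculation (3.9):** 50 patients, 25 per group, are said to be capable of "detecting a 30% difference in improvement of the primary outcome (TUG and TSMB"), "with an alpha error of 0.05 and beta error of 0.2". One alpha is given for the pair, with no split.
- **Statistical analysis (3.13):** "Statistical significance will be established as *P* < .05". The only multiplicity device is that "multiple comparisons will be analyzed with the Tukey test", attached to the repeated-measures ANOVA.
- **Discussion (4):** after naming balance and mobility as primary, and anxiety and depression as secondary, the article describes what would let professionals recommend one orthosis: "If 1 of the AFO types is proven to be superior to the other in some of these aspects".

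No section says whether one primary or both must succeed.

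**The concern.** With two primary tests, 0.05 on each test is not 0.05 for the trial unless a rule links them. Tukey adjusts among group and time means within one outcome; it does nothing between TUG and TSMB. The Discussion leans towards accepting a win on part of the outcome set. Read together, these sections let a chance result on one of two primaries lead to a recommendation, at an error rate above the one used to size the trial.

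The stake is the trial's stated purpose, which is to identify the more suitable orthosis and help standardize prescription. With 25 patients per group, one false-positive primary could decide that recommendation.

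**Working it through.** **Inputs.** Two primary outcomes (3.7); alpha 0.05 and beta 0.2 (3.9); threshold 0.05 (3.13); 25 per group (3.5). Assumed, because not stated: two-sided tests (the main hypothesis in the Introduction is that the types differ), one between-group test per outcome, and a correlation ρ between the two test statistics, shown over a range.

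**1. The plan's own figure.** N = 50 can be neither confirmed nor refuted, because 3.9 gives no SD, base rate or sidedness. What 25 per group detects with 80% power at two-sided 0.05 is:

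- normal approximation: (1.960 + 0.842) × √(2/25) = 2.802 × 0.2828 = 0.79 SD
- t-test: 0.81 SD

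A 30% difference therefore matches 25 per group only if the SD is about 0.30/0.79 = 38% on the same scale (37% by the t-test).

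**2. Either primary suffices.** The chance of at least one false positive is 1 − P(|Z₁| < 1.96 and |Z₂| < 1.96). For independent tests this is 1 − 0.95² = 0.0975. For correlated tests it comes from the bivariate normal distribution:

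| ρ (assumed) | At least one false-positive primary |
|---|---|
| 0 | 9.8% |
| 0.5 | 9.1% |
| 0.7 | 8.4% |
| 0.8 | 7.8% |
| 0.9 | 7.0% |
| 1 | 5.0% |

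The rate equals 5% only under perfect correlation. The upper bound is 0.05 + 0.05 = 10%.

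**3. Both primaries required.** Alpha stays at or below 0.05. If each test has 80% power, joint power is P(Z₁ < 0.842 and Z₂ < 0.842):

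| ρ (assumed) | Power to win on both |
|---|---|
| 0 | 0.80² = 64% |
| 0.5 | 69% |
| 0.8 | 73% |

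All three are below 80%.

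**4. After a Holm correction.** The smaller P value is compared with 0.025 and, if it passes, the other with 0.05. The chance of any false-positive primary is at most 5% (for independent tests, 1 − 0.975² = 4.9%). At 25 per group:

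- a difference with 80% power at 0.05 (0.81 SD) has about 71% power per outcome at 0.025 (70.6% by t-test, 71.2% by normal approximation)
- the difference detectable with 80% power at 0.025 is about 0.90 SD (t-test)
- keeping 80% per outcome at 0.025 for the 0.81 SD difference would take about 31 per group, 62 in total before dropout. Holm itself does not require this increase.

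**The case against.** **Silence.** This is a condensed article, and a rule for sharing alpha across two primaries is often left to an analysis plan, which is not shown. That would answer a pure omission. Here, though, the article itself fixes two primaries, one alpha, one threshold and a partial-success standard. A later rule that controlled alpha would still leave 3.9 and the Discussion to be reconciled with it.

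**The both-must-win reading.** Section 3.9 uses the singular for TUG and TSMB together, which could mean that both are required. No section says so, and the Discussion points the other way. If it is what was meant, the alpha complaint disappears and the power shortfall in step 3 takes its place.

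**The Discussion is not a decision rule.** This stands in part. The sentence concerns clinical implications and says some, not any; it sets no number. It is still the only indication of which result would lead to a recommendation. Nor does 3.9 call 0.05 a trial-wide rate, so the size of the problem has to be given conditionally on the success rule.

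**Stronger readings that a reader might infer.** Two go beyond the documents.

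- Counting all eight listed instruments as routes to a recommendation gives 1 − 0.95⁸ = 34% if independent. The Discussion names only balance, mobility, anxiety and depression in this context. The other instruments are declared secondary in 3.8, and unadjusted testing of secondary outcomes is ordinary.
- Concluding that TUG must become the sole primary because it is timed while TSMB is scored by an observer. The documents do not settle that choice: TSMB carries the dedicated balance score, and TUG is a performance test in unblinded patients. The trial is registered and recruitment was ongoing at submission, so demoting a primary outcome would be more than a change of wording.

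The claim that the error rate nearly doubles is also only the low-correlation end. Both instruments assess mobility and balance, so a substantial correlation is plausible.

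**Conclusion.** The concern holds in conditional form. If a win on either TUG or TSMB suffices, which is where the article leans, the chance of at least one false-positive primary is about 7% to 10% (correlation 0.9 down to 0), not the 0.05 used in 3.9. If both are required, alpha holds but power is about 64% to 73% (correlation 0 to 0.8), not 80%. Either way, one of the two error figures in 3.9 does not describe the design.

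This rests on two-sided testing, one between-group test per outcome, and assumed correlations; step 3 also assumes 80% power on each test. The documents do not show that secondary results formally count as success. They only leave that open, because the Discussion mentions anxiety and depression in the same context.

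**What to change.** 1. In 3.7 and 3.13, keep TUG and TSMB as the two primaries and state that they are tested with Holm at an overall two-sided 0.05: the smaller P value against 0.025, then the other against 0.05.
2. Restate 3.9 to match: with 25 per group, a difference of about 0.81 SD has about 71% power per outcome at 0.025, and the difference detectable with 80% power at 0.025 is about 0.90 SD.
3. In 3.13 and the Discussion, state that secondary outcomes are supportive and that a secondary result alone does not support recommending one orthosis.

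**Cost.** No extra patients and no change of primary outcome. The smaller P value must now meet 0.025, and the stated per-outcome power is less favourable than 80%. The rule should be set before the outcome data are analysed.
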